## **The trial protocol**

### **Title: A community-based health intervention trial to increase attendance to the national cervical cancer screening program among immigrants in Norway.**

#### **1. Relevance relative to the call for proposals**

Equity is a cornerstone of the Norwegian health care system. However, there is evidence that there are barriers for immigrant women to access cancer screening programs. This in turn contributes to later diagnosis, worse prognosis and higher utilization of resources among immigrant women with cancer. Although health-related interventions should become increasingly diversity-sensitive [1], adapting services to the individual cultural and religious background is still necessary to reduce health inequalities and provide cost-effective health care and is dependent on the active involvement of users.

In this proposal we present a community-based health intervention trial aimed at increasing participation of immigrant women to the existing cervical cancer-screening program. After a review of the literature and relying on analyses conducted by the research group identifying lower attendants to cervical cancer screening in Norway [2], women from Somalia and Pakistan were selected for the intervention. For this project, we will first invite immigrants from Somalia and Pakistan to identify barriers and factors that influence their attendance to screening of cervical cancer in Norway; then, together with the stakeholders we will develop an adapted intervention based on the existing literature and identified factors; this intervention will be subsequently implemented among women from Somalia and Pakistan and then evaluated using both linked Norwegian registries and qualitative process evaluation. Health-economic analyses will also be conducted.

This community-based study has a parallel trial financed by the Norwegian Cancer Society (2015-2019) with the same aim but targeting health personal that will be conducted in another region in Norway. Taking advantage of this, we propose to conduct a systematic comparison of both interventions. Our health economic analyses will assess the acceptability, equity- and efficiency implications of both interventions. Thus, our proposal will provide new practice-based knowledge and a firmer evidence base to improve public health through the development of health prevention interventions with potential for national implementation within the most common cancer-screening program in Norway. Our design incorporates user involvement from the very beginning of the project and through several stages. It includes an interdisciplinary project group and builds upon cross-sectorial cooperation.

#### **2. Aspects relating to the research project**

##### **A. Background and status of knowledge**

###### ***A.1 Immigrants in Norway***

Over the last decade, there has been a rapid increase in international migration to Norway. Immigrants comprise around 16% of the total population of Norway in 2016. They come from 223 different countries and regions and are younger than Norwegian-born, with over 50% being aged between 20 and 40 years. There are immigrants in all Norwegian municipalities, with higher percentages in Oslo, where immigrants and their descendants make up 32,5 % of the population. Among non-European immigrants, the major immigrant group comes from Somalia, followed by Iraq, Philippines and Pakistan. Immigrants from Somalia are mostly refugees who have lived in Norway for a relatively short period of time, while those from Pakistan have lived in Norway for a long time and have the highest number of descendants in Norway [3].

###### ***A.2 Immigration and cancer***

The incidence rates for most cancers are low in developing countries, but for a few cancers, including cervical cancer, the rates are high [4]. Migration studies have found that the risk of cancer change when people move, especially when they move from low-incidence to high-

incidence countries [5]. As migrant populations represent a minority in the host country, unless the host country specifically monitors and targets cancer risk among minority groups, important health care needs among these new immigrants can easily be overlooked [6].

Women comprise about 50% of the global international migrants (95 million) [7]. However, only recently have policy and decision makers started to acknowledge the complexity of the immigrant health and the risks that migrant women can face in the receiving countries [7, 8]. The health issues in immigrants are complex, and a better understanding of cancer in immigrants to Europe and in particular changes in cervical cancer risks is necessary [9, 10] to develop preventive strategies.

#### **A.2.1 The Norwegian Cervical Cancer Screening Program**

The Norwegian Cervical Cancer Screening Program (NCCSP) aims to reduce the incidence and mortality of cervical cancer through identifying and treating early cancer stages, which if left untreated have a high likelihood of progressing to invasive cancer. It was implemented in 1995, and it is based on triennial screening with cytology smears among women aged 25-69. Women with no registered screening test during the last three years receive a reminder letter from the Norwegian Cancer Register with a recommendation to make an appointment with their general Practitioner (GP) to have a smear. Overall, 76% of the women have taken a smear after two reminders [11]. While the letters and reminders raise the attendance for the general population, their effectiveness among immigrants is unknown. The screening programme in Norway does not explicitly target immigrant women and hence they are usually under-recruited and not represented at the population level. Yet another constraint is that the reminders are sent in Norwegian, which might dissuade immigrant women from participating in screening or health intervention programmes. According to the Cancer Registry of Norway, more than half of the women diagnosed with cervical cancer have rarely or never taken a Pap test. The NCCSP is changing the test stepwise in Norway, but the type of test taken by the health professional will not affect the results of our study.

#### **A.2.2 Immigration and cervical cancer screening**

Cervical cancer is preventable and has a good prognosis if detected early. Although cervical screening has reduced the incidence in many high-income countries, the incidence remains high in countries that do not screen [12]. In accordance to other European countries pointing to low attendance among immigrants, and challenges to access at both the user level and the host health system level [13-15], our research group has newly stated for the first time in Norway that immigrant women, especially from Asia and Africa, are underrepresented in the smears taken at the GP office in Norway [2]. Low attendance to screening programs in turn can result in higher occurrence of cervical cancer in immigrant groups [14] and poor prognoses due to diagnosis at a late stage of cancer, otherwise preventable.

From the *users' point of view*, participation in cervical cancer screening [16] might be influenced by barriers such as fatalistic attitudes, lack of knowledge, fear of cytology smears threatening one's virginity, beliefs that a cytology smear is unnecessary unless one is ill or has risky sexual behaviours, as well as stigmatization within their community and providers [13]. Within the *host health system* barriers such as lack of adequate information for users, language, difficulties in access to health care and varying cultural competence among health workers may prevent new immigrants from following the screening guidelines [17]. However, barriers probably vary among different immigrant groups and in relation to the host country. Therefore, a better understanding of potential cultural, social and other structural barriers to cervical cancer screening programs for different groups of immigrant women in Norway is an essential prerequisite to design culturally appropriate health promotion strategies and screening interventions. The solutions that address these barriers could effectively promote better awareness and encourage women to attend screening, thus diminishing inequity in service utilisation compared to the native Norwegian population.

In this regard, one strategy that has been found to increase cancer-screening participation is by engaging health providers to motivate and directly communicate with women [18, 19]. At the user level, the use of “promoters” (female educators specially trained in the community) has been positively evaluated although the effect to change behaviours has not been evaluated at the population level [20]. Reflecting on these observations, this project will develop and compare two interventions. One intervention involving providers (health personnel) is already under development, financed by the Norwegian Cancer Society. The other one, that we apply funding for, will involve the users (immigrant women), to increase their participation in the cervical cancer screening program in Norway.

## **B. Approaches, hypotheses and choice of method**

### ***B.1. Approaches and hypothesis***

Individual lifestyle factors are influenced by social and community networks, as well as general socio-economic, cultural and environmental conditions [21]. There are several bricks that have to be in place to attain high attendance to screening tests among immigrants. From a *community point of view*, not only women individually need to be aware of the availability of the tests and their benefits and pitfalls, but also the opinion of the other members of the community about taking the tests and the associated barriers to access. Regarding *health practitioners*, they should especially offer the test to the groups with low attendance to screening and high cancer risk, as is the case with some immigrant groups, and to know how to do this in a culturally appropriate way.

Our primary hypothesis is that well developed user targeted and health professional targeted community-level interventions will increase cervical cancer screening attendance rates among immigrant women. Although strategies targeting users and health professionals are thought to be complementary [22], no study to date has compared the effect of each of the approaches to increase participation to screening of cervical cancer. Furthermore, no study to date compares the cost-effectiveness and equity implications of user targeted and health professional targeted interventions for immigrant populations in Norway.

### ***B.2. Goals and objectives***

This study is composed by four work packages (WP) of which we apply for founding for three of them (WP1, 3 and 4) while WP2 is already running, financed by the Norwegian Cancer Society (2015-2019).

WP1- *User-targeted* intervention study in Akershus and Buskerud designed to evaluate the effect of a community-based intervention targeting women from Somalia and Pakistan to increase their attendance to the national cervical cancer screening prevention program. The effect will be measured both quantitatively by means of linked national registries and qualitatively through focus groups and in depth interviews.

WP2- *Health professional-targeted* intervention study in Hordaland designed to evaluate the effect of a community-based intervention targeting GPs, midwives and private gynaecologists to increase their awareness and knowledge about immigrants and cervical cancer screening. The effect will be measured both quantitatively and qualitatively.

WP3- *Comparison of interventions*. To compare the effect of the interventions described above (WP1 and WP2) measured quantitatively (effect size) and qualitatively (how the interventions work). In this way, we will create evidence to guide priority setting.

WP 4- *Cost-analyses* of each of the interventions (WP1 and WP2) will be performed, and cost-effectiveness considered by calculating incremental costs- incremental effectiveness and incremental cost-effectiveness. We will consider equity impact by assessing the distributional consequences for health care utilisation.

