### Area and sample size

This intervention will be implemented in Akershus and Buskerud. These counties are chosen based on the existence of enough immigrants but avoiding areas known to have low participation rates due to on-going research programs in other health fields. Sample size is calculated for an increase in cancer screening participation from 0.45 to 0.55 with 80% power and 5% significance level. After trying several intra class correlation (ICC) levels, we decided to divide four municipalities in Akershus and Buskerud (Asker, Bærum, Lørenskog and Drammen) in 16 clusters that were matched according to the calculated number of female immigrants aged 20 to 66 from Somalia and Pakistan. To avoid contamination, after assuring that pairs were not naturally linked by a mosque or other natural known gather centre for these populations, clusters will be randomly assigned to intervention or control groups (matched pair randomization) [25].

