### WP2- Heath professional intervention (not included in this application)

A similar process is being used since 2015 to develop the *Heath professional intervention*, but interviewing health professionals. Bergen was divided into 20 clusters according to the 20 geographical subareas defined by Statistics Norway and similar calculations and matched pair randomization to those described above were conducted. All GPs, midwives and private gynaecologists working in the intervention cluster areas will be assigned to the intervention group; similar health professionals working in the other municipalities will be chosen as controls. This intervention will be implemented in Hordaland (Bergen) in autumn 2016 to increase awareness of the health professionals involved in screening working in the chosen municipalities. No change in “screening as usual” will be implemented for health professionals working in the control areas. Our experience in this process will facilitate work related to WP1.

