### **3.1 Timeline**

In this Timeline we present the whole project, also parts of the WP2 for better understanding (in cursive means not included in this proposal).

2017

1. Pre-intervention focus groups with Somali and Pakistani women (WP1, Paper 1)

2. Development of User strategy, recruitment and training of peer educators in Akershus/Buskerud from Somalia and Pakistan (WP1, Paper 2)
  3. Implementation User strategy with Somali and Pakistani women (WP1)
  4. Development and registration of cost (WP4)
  5. *Post-intervention Health professional interviews in Hordaland (WP2)*
- 2018
1. Writing papers 1 and 2 (WP1)
  2. Post-intervention interviews in Akershus/Buskerud (WP1, Paper 3)
  3. *Analyses post-intervention register data in Hordaland (2016-2018): attendance to cytology after the Health professional intervention (WP2)*
  4. Cost-effective analyses Health professional intervention (WP4, Paper 1)
- 2019
1. Analyses post-intervention register data in Akershus/Buskerud (2016-2018): attendance to cytology after the User intervention (WP1, Paper 4)
  2. Writing papers 3 and 4 (WP1)
  3. Cost-effective analyses User intervention (WP4, Paper 2)
  4. Comparison of interventions, qualitative approach (WP3, Paper 1)
- 2020
1. Comparison of interventions, quantitative approach (WP3, Paper 2)
  2. Cost-effective analyses: comparison and priority of interventions (WP4, Paper 3)
  3. Dissemination of results to communities, stakeholders and policymakers.

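### WP3 compares the effect sizes of two separate trials that differ in region, target population and exposure time, with limited precision, to guide priority setting

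*Protocol*

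**What the plan says.** Section 1 introduces the parallel trial and announces the comparison: "Taking advantage of this, we propose to conduct a systematic comparison of both interventions". B.2 defines the quantitative part of WP3: "To compare the effect of the interventions described above (WP1 and WP2) measured quantitatively (effect size"). It then gives the purpose: "In this way, we will create evidence to guide priority setting". The Timeline (3.1) lists for 2020 "Comparison of interventions, quantitative approach (WP3, Paper 2"), followed by a WP4 paper that compares and prioritises the interventions on cost-effectiveness.

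The two trials differ as follows.

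- **Region and units.** WP1 randomises 16 matched clusters in four municipalities of Akershus and Buskerud (Area and sample size). WP2 uses 20 subareas of Bergen (WP2 section).
- **Target.** WP1 is for women from Somalia and Pakistan (B.2, Participants). WP2 works through GPs, midwives and private gynaecologists and concerns immigrants, with no country of origin named (B.2).
- **Start.** For WP2: "This intervention will be implemented in Hordaland (Bergen) in autumn 2016". WP1 is implemented in 2017, after focus groups, development and training (Timeline).
- **Outcome window.** The Timeline labels the register data 2016-2018 for both.

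The only sizing statement is for WP1: "Sample size is calculated for an increase in cancer screening participation from 0.45 to 0.55 with 80% power and 5% significance level". For WP2 the protocol says only that the calculations and the matched-pair randomisation were similar.

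**The concern.** Each trial has a randomised contrast within its own region, but the step from two effects to a preference between interventions is not randomised. Three features other than the intervention can then drive a difference in effect size.

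1. **Exposure time.** In a shared calendar window, the intervention that starts later has fewer exposed months in which to raise attendance.
2. **Population.** The response may differ between Somali and Pakistani women and a broader group of immigrants.
3. **Region.** Access to services and local practice may modify the effect.

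In addition, each trial is planned around its own effect, so the difference between the two estimates is less precise than either one. The statement at stake is which intervention should have priority, together with the WP4 comparison that follows. The estimate of WP1 against its own controls is not affected.

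**Working it through.** **Inputs.** Attendance 0.45 against 0.55, 80% power, 5% significance (Area and sample size); two-sided testing is assumed. 16 clusters, from "in 16 clusters that were matched according to the calculated number of female immigrants aged 20 to 66 from Somalia and Pakistan". Women: 625 + 915 = 1540, about half in intervention clusters, so 770 per arm and m = 1540/16 = 96.25 per cluster (Participants). The ICC is not given; the text says only "After trying several intra class correlation (ICC) levels". I show a range of 0 to 0.05 as an assumption. The number of women in WP2 is not given; its precision is assumed equal to that of WP1. Normal quantiles are used throughout.

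**Step 1: the plan's own figure.** Without clustering, n per arm = [1.960 x sqrt(2 x 0.5 x 0.5) + 0.842 x sqrt(0.45 x 0.55 + 0.55 x 0.45)]^2 / 0.10^2 = 392. The design effect is 1 + (m - 1) x ICC. The largest ICC that 770 per arm can carry is (770/392 - 1)/95.25 = 0.0101. At ICC 0.01 the design effect is 1.9525 and power is 80.3%. The stated 80% is therefore consistent with an ICC near 0.01. It cannot be strictly reproduced, because the ICC used is not stated.

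**Step 2: what unequal exposure alone could do (illustration).** Assume a constant screening hazard, a three-year window, and full effect from the start date.

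- Control hazard: -ln(0.55)/3 = 0.1993 per year. Intervention hazard: -ln(0.45)/3 = 0.2662 per year. Ratio 1.34.
- With e exposed years in the window, the difference in attendance is 0.55 x [1 - exp(-0.0669 x e)].
- e = 2.25 (WP2): 7.7 points. e = 1.5 (WP1): 5.3 points. e = 1.25 (WP1): 4.4 points.

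The same hazard ratio in both trials would thus show a gap of 7.7 - 5.3 = 2.4 to 7.7 - 4.4 = 3.3 points.

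**Step 3: precision of the difference of effects.**

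- SE of one effect at 80% power for 10 points: 10/(1.960 + 0.842) = 3.57 points.
- SE of the difference: 3.57 x sqrt(2) = 5.05 points.
- 95% CI half-width: 1.960 x 5.05 = 9.9 points.
- True difference with 80% power: 2.802 x 5.05 = 14.1 points.
- Power at a true difference of 5 points is 17%; at 10 points, 51%.

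**Step 4: sensitivity.** With 770 per arm, SE of one effect = sqrt(2 x 0.2475 x design effect/770), and the same SE is used for WP2:

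| ICC | WP1 power for 10 points | SE of one effect (points) | CI half-width of the difference | True difference with 80% power |
|---|---|---|---|---|
| 0 | 97.6% | 2.54 | 7.0 | 10.0 |
| 0.005 | 89.9% | 3.08 | 8.5 | 12.2 |
| 0.01 | 80.3% | 3.54 | 9.8 | 14.0 |
| 0.02 | 63.5% | 4.32 | 12.0 | 17.1 |
| 0.05 | 37.2% | 6.09 | 16.9 | 24.1 |

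At ICC 0.01, a WP2 standard error of 0.5 to 1.5 times that of WP1 gives 11.1 to 17.9 points.

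**The case against.** The strongest reply has four parts.

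**Much is already provided for.** Each effect has its own matched-pair randomised controls. Country of origin, length of stay and socioeconomic variables are available for adjustment (B.3.2), and there is a baseline from 2012 (B.3.3). The WP4 model is to assess uncertainty and whether it could alter policy recommendations. This stands in part. Within-region controls and baseline data deal with imbalance and secular trend. They do not make the exposure times equal or the populations the same, and an uncertainty analysis carries sampling error without by itself removing such a misalignment.

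**The exposure gap is inferred.** No start month is given for WP1; 2017/3 is an item number in the Timeline, not a quarter. The Hordaland register analysis is listed under 2018, so its data may end before December 2018, which would narrow the gap. This stands: the 2 to 3 points are an illustration. Equal follow-up is still not secured by dates that start one intervention in 2016 and the other in 2017 under one window label.

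**The precision figure is conditional.** WP2 has 20 clusters, a possibly broader population, and no stated number of women or planned effect. It could be more precise than WP1. This stands, and the range above reflects it.

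**Method detail belongs in a statistical analysis plan.** That is true of the model and the adjustment set. The protocol itself, however, fixes the comparison, its purpose, the start dates and the windows, and these do not fit together.

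**Conclusion.** The point holds in a limited form. Followed as written, WP3 mixes intervention effect with exposure time, population and region. Under the stated assumptions, exposure alone could shift the comparison by about 2 to 3 points. If both trials have just their planned precision, the 95% CI for the difference is about +/-10 points, with 80% power only for a true difference of about 14 points (about 10 to 24 for ICC 0 to 0.05).

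Two stronger readings are not supported:

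- A reader might infer that WP3 cannot separate the interventions unless they differ by 14 points. That is wrong. Fourteen points is the true difference detectable with 80% power; an observed difference of about 10 points would already be significant, and a true 10-point difference would be detected about half the time.
- A reader might infer that the sponsor will rank the interventions on separate p-values, or take a non-significant difference as equivalence. The protocol says neither.

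**What to change.** 1. Describe WP3 in B.2 as a non-randomised indirect comparison.
2. Estimate each effect against its own randomised controls, over the same number of months from each intervention's start. State both start months and both data cut-offs. Clarify the WP2 controls as well: that section randomises subareas of Bergen but places the control professionals in other municipalities.
3. Use a common population: Somali and Pakistani women in both regions, or WP2 standardised to the WP1 nationality mix. First confirm that the origin coding allows this, because the ethics section says that origin will be requested only in broad groups.
4. Report the difference of the two effects with its CI. State its limited precision conditionally, with the ICC and the WP2 size that it rests on. Do not write that differences below 14 points cannot be resolved.
5. Use the aligned estimates and their uncertainty in the WP4 comparison.

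The cost is mainly wording and analysis, since the register request already covers dated tests for all women in Norway. The price is a more modest claim, and fewer Bergen women or fewer follow-up months in the matched comparison.
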